## Abstract

(1) *Background*: Obesity is a global health problem, and its prevention must be a priority goal of public health, especially considering the seriousness of the problem among children. It is known that fetal and early postnatal environments may favor the appearance of obesity in later life. In recent years, the impact of the programs to prevent obesity in childhood has been scarce. The aim of this research is to evaluate the effectiveness of an intervention based on the concept of early programming. (2) *Methods*: Non-randomized controlled trial design. Inclusion criteria are: two-year-old infants whose gestational period begins in the 14 months following the start of the intervention, and whose mothers have made the complete follow-up of their pregnancy in the same clinical unit of the study. The intervention will be developed over all the known factors that affect early programming, during pregnancy up to 2 years of life. Data will be collected through a data collection sheet by the paediatricians. A unibivariate and multivariate analysis of the data will be carried out. (3) *Ethics and dissemination*: The trial does not involve any risk to participants and their offspring. Signed informed consent is obtained from all participants. Ethical approval has been obtained. (4) *Results*: It is expected that this study will provide evidence on the importance of the prevention of obesity from the critical period of the first 1000 days of life, being able to establish this as a standard intervention in primary care.

## 1. Introduction

Obesity is a global public health problem, and it has been declared the epidemic of the 21st century by the World Health Assembly [1] because of its high prevalence and its association with other chronic diseases [2,3]. The development of preventive strategies must be a priority goal of public health in order to decrease the social and economic burden of obesity [4].

The situation is even more concerning among children, due to its high incidence in developed countries, the appearance of excess weight at younger ages [5,6] and the fast increase in the prevalence of childhood obesity in emerging countries [7].

Childhood obesity is recognized as a disease by the World Health Organization. It is also associated with other pathologies and can lead to psychological damage [8]. The high prevalence of obesity in childhood and adolescence becomes a problem for the health system, since a large proportion of overweight children will be obese in their adulthood [9].

In addition, inequalities in obesity have risen, with greater increases in the prevalence of obesity in the most disadvantaged social groups [10], so that obesity is a marker of social inequalities in health [11].

In Spain, the latest data in school children [12] show a high prevalence of excess weight, with a significant reduction in overweight, but not in obesity [13]. In order to fight against diseases whose causes are related to exposure to social and environmental factors, such as obesity, preventive measures provide the best results. In recent years, programs to prevent childhood obesity have been developed [14,15,16]. However, the effects of these programs on the child population have been scarced in scope [12]. In this sense, in order to confront these results, some authors propose a change in the approach of strategies to prevent childhood obesity [17,18].

Recent knowledge about early programming offers the opportunity to develop new prevention strategies. The concept of early programming has been incorporated into the prevention recommendations for childhood obesity [19,20]. These new strategies should be focused on the maximum-plasticity period of early programming, before and during pregnancy and in the first 2–3 years of postnatal life. This period is critical both for development and for the prevention of childhood obesity.

A systematic review [21] of interventions aimed at preventing childhood obesity, developed in pregnancy and the first 2 years of life, only found effectiveness in interventions based on the protein content of the formulas or in behavioral interventions focused on parents about nutrition and responsible feeding.

Another systematic review of interventions during the first 1000 days found a total of 26 interventions [22]. Two were only developed during pregnancy, and were not effective. Six began during pregnancy and continued in the postnatal stage. Of these, those involved in only one aspect (breastfeeding promotion, nutritional supplements) were not effective. Two interventions, based on home visits and group sessions focused on diet, infant feeding practices and physical activity, proved effective on BMI at 12 or 24 months. Therefore, it is desirable that interventions take place over the entire 1000-day period and encompass as many aspects as possible related to the risk of childhood obesity.

The fact that an early exposure to environmental factors could influence the health of the offspring in future life has been recognized from the first half of the 20th century, with the epidemiological studies of Kermack [23]. Later, Barker formulated the hypothesis of the fetal origin of adult diseases, which relates the incidence of certain adult diseases to an environment of malnutrition within the uterus [24]. Early programming is considered an adaptive response to the environment, based on the information received during fetal life and the first years of postnatal life [25].

Several studies in humans and animal models propose different early programming mechanisms [26,27,28]. In recent years, there has been great interest in the role of epigenetics. This is defined as the set of non-genetic factors that induce heritable changes in the expression of genes without altering the sequence of the genome [29]. This susceptibility to early programming is limited to a critical period of development, especially in fetal life and the first 2–3 years of postnatal life [30,31].

Several early programming factors (EPF) have been associated with childhood and adult obesity. They can be classified into pre- and post-natal factors:

Prenatal: maternal overweight or obesity [32,33,34], excessive weight gain during pregnancy [34,35,36], gestational diabetes [37,38], maternal malnutrition [39,40,41] and maternal smoking [42,43].

Postnatal: short breastfeeding [44], rapid weight gain in the first year of life [45], excess protein intake [5,46], vitamin D deficiency [47,48], and caesarean section (where there is evidence for and against) [49,50,51].

Other factors, related to lifestyle and family eating behaviors, have also been linked to an increased risk of obesity in childhood: appetite control [52,53], sleeping habits [54], quality of maternal-child relationship [55] and other modifiable factors like screen time, physical activity [56], complementary feeding [57], etc. 

The accumulation of these early programming factors in the same individual is associated with a progressive risk of obesity at 6 years old [58,59] or at 7–10 years old [60], regardless of what these factors are. Although all factors that are associated with childhood obesity cannot be controlled, the decrease in the number of factors that accumulate in an individual could reduce the obesity risk.

Accordingly, prevention strategies are more effective the earlier they have been developed in the life course. Therefore, we have developed strategies that are implemented from the prenatal stage until 2 years old. The concept of early programming must be used alongside the prevention opportunity, with a positive message that obesity prevention is possible by decreasing the number of programming factors. In this project, we want to carry out a realistic intervention, developed entirely in primary care by the usual health team. It must be acceptable to primary care professionals and supported and endowed with resources by the health administration. It also must be integrated into the routine practice of the Andalusian Children and Adolescents Health Program (A-CAHP) and Care Process of Pregnancy, Childbirth and Puerperium (CPPCP) controls, taking advantage of the high number of visits planned in these programs, so that it can, if proves to be effective, generalize to routine activity in primary care. 

The project’s global hypothesis is that an intervention in the first 1000 days of life on the early programming factors related to childhood obesity will achieve more adequate early programming and will decrease the prevalence of childhood obesity. The risk of developing obesity in childhood will be lower when the number of factors accumulated in the individual in this critical first phase is decreased. This improvement in early metabolic programming will be reflected in a lower percent of body fat mass at 2 years of age, compared to the control group.

The aim of the project is to evaluate the effectiveness of a combined multifactorial educational and care intervention for preventing obesity and overweight in childhood, based on the concept of early programming, and developed during pregnancy and the first 2 years of life (the first 1000 days) by a multidisciplinary group in primary care. The specific objectives are:

To analyse the body fat mass at 2 years of age in a control group of children who reach this age between November 2017 and June 2019, belonging to two pediatric quotas of the Basic Health Zone (BHZ) of Puerto Real.

To analyse the body fat mass at 2 years of age in the intervention group of children, whose pregnancies begin between January and December 2018, belonging to four pediatric quotas of the BHZ of Puerto Real. 

To compare the body fat mass at 2 years of age between the control and intervention groups.

## 2. Materials and Methods 

### 2.1. Study Design

This study is a quasi-experimental design with two groups (control and experimental group), in which the results on body fat in 2-year-old children, obtained after a combined educational and care intervention, are compared with those obtained after the usual intervention developed in our Clinical Management Unit (CMU). 

Randomization could not be carried out for ethical reasons; once the intervention has begun, we should not deprive a part of the population of it. Similarly, as it is a small town, there could be contamination between groups (transfer of information). Therefore, a historical control group of the same population consisting of children who turn 2 years old during 2018 will be used.

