### 2.4. Recruitment

A single midwife will take charge of maternal education in the CMU Puerto Real, which includes the Ribera del Muelle Health Centre where there are three paediatricians, and the Rio San Pedro Health Centre where there is one. Therefore, all pregnant women will receive exactly the same information about the intervention. After birth, the parents will decide in which of the six paediatricians of the BHZ of Puerto Real they will register their children, and we cannot interfere in that decision.

The study population of the control group will be constituted by two-year-old children of two quotas of the Basic Health Zone of Puerto Real. The paediatricians have employment stability for at least the expected duration of the study and have agreed to participate. The inclusion in the study and the data collection will be carried out in the health controls at 2 years of age at the same time as the intervention in pregnant women begins, so that neither mothers during pregnancy nor infants after delivery will have been influenced by the intervention. Once the intervention ends, their results will be analyzed from the data obtained from the mother–child pairs.

Following the above criteria, all newborns assigned to the four pediatricians of the unit that meet the inclusion criteria will be included in the intervention group. Two paediatricians from the same unit will also participate in the data collection for the control group. Including a greater number of pediatricians is necessary to obtain the calculated sample of the intervention group, due to the decrease in the birth rate observed in recent years. Inclusion in the study will be done at the first pediatric visit of the newborn.

The inclusion criteria are: two-year-old infants whose pregnancy begins in the 14 months following the start of the intervention, and whose mothers have made the complete follow-up of their pregnancy in the Care Process of Pregnancy Childbirth and Puerperium and begun the monitoring of child health controls of the Andalusian Children and Adolescents Health Program in our unit. The exclusion criteria are: infants whose parents do not authorize their participation in the study in writing.

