### 2.7. Intervention 

The intervention is being carried out during pregnancy and the following 2 years after birth. The intervention period during pregnancy began, for each individual patient, when they went to their first visit related to the Care Process of Pregnancy, Childbirth and Puerperium Program during the period of time between January 2018 and February 2019. This first visit is carried out by the midwife in charge (Clinical Managing Unit) and is integrated within the standard medical visits and workshops, although reinforced by a specific workshop, purely based on the intervention scheme, at the beginning of the patient’s pregnancy. 

Three workshops take place during this period. They happen once a month for a total of two hours at a time. In each workshop, the patients are handed a fully informed leaflet in which they can learn about the information given and write personal notes at their discretion. 

Workshop number one, specifically created for the intervention period, takes place before the 12th week of pregnancy is reached. To begin the workshop, a 15- to 20-min slideshow is shown to explain the “early programming” concept and its close relation to childhood obesity. Immediately after this, the attendees will be fully informed about the importance of physical exercise, quitting toxic habits and creating a healthy eating plan for the entire family. 

At the second workshop, which has to be completed between the 16th and 18th weeks of pregnancy, the information provided is related to the specific healthcare and healthy habits that a pregnant woman should embrace, considering the changes she will experience.

Finally, on the third workshop, carried out between the 30th and 32nd weeks of pregnancy, the attendees will learn about the special characteristics of care related to newborns. To begin, a 20-min slideshow, in which the postnatal programming and its different factors are explained in detail, will be shown. After that, exclusive breast feeding will be explained and promoted as the preferable option. The child and adolescent health scheme planed by the Andalusian health authorities will also be introduced during this session. 

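### Both groups' entry windows are stated in conflicting versions, and the assurance that controls are uninfluenced is unsupported for infants measured late

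*Protocol article*

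**What the plan says.** **Controls.** The specific objectives (1. Introduction) analyse "a control group of children who reach this age between November 2017 and June 2019", drawn from two paediatric quotas. Section 2.1 instead says that "a historical control group of the same population consisting of children who turn 2 years old during 2018 will be used". Section 2.4 adds that controls are included and measured at their 2-year check, at the time the intervention in pregnancy starts, "so that neither mothers during pregnancy nor infants after delivery will have been influenced by the intervention".

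**Intervention group.** The objectives take children "whose pregnancies begin between January and December 2018". The inclusion criterion in 2.4 takes infants "whose pregnancy begins in the 14 months following the start of the intervention", and the abstract agrees. Section 2.7 places the first pregnancy visit "during the period of time between January 2018 and February 2019" and puts that visit at weeks 4–7.

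**Setting.** Section 2.1 gives the risk of contamination in a small town as one reason for using historical controls. Section 2.4 has two paediatricians of the intervention unit also collecting control data, and 2.3 accepts that those delivering the intervention cannot be blinded.

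**The concern.** In a non-randomised comparison with historical controls, the entry dates are the allocation rule. If they are stated in two versions for one group and three for the other, the document does not say who is being compared. The control window could then be settled after data are in hand.

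The second issue is timing. The case for uninfluenced controls rests on measuring them as the intervention starts. If control measurement runs on while the same unit is already following intervention newborns, that premise no longer covers every control child. The protection that the historical design was meant to give is then weaker for those seen late.

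**Working it through.** **Inputs.** 50 newborns per quota per year (2.2); two control quotas (objectives) and four intervention quotas (objectives, 2.4); 100 controls and 150 experimental units planned, 15% loss, 320 births (2.5); first visit at weeks 4–7 (2.7). Assumption not in the document: birth at 40 weeks.

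**The plan's own figure.** Two quotas × 50 × 1 year = 100, the planned control number. After 15% loss this is 85. The stated precision follows from 1.96 × √(0.25/n) × √((320 − n)/319): n = 85 gives 9.1%, and n = 150 × 0.85 = 127.5 gives 6.7%. These are the protocol's 9% and 7%, though with the group labels the other way round. So 100 is a number before losses, and 85 is already planned for.

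**Children available under each version** (quotas × 50 × months/12, before refusals and the other eligibility criteria):

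| Group and rule | Months | Available | At 320/6 births per quota |
|---|---|---|---|
| Control, 2018 only | 12 | 100 | 107 |
| Control, Nov 2017–Jun 2019 | 20 | 167 | 178 |
| Intervention, pregnancy start in 2018 | 12 | 200 | 213 |
| Intervention, pregnancy start within 14 months | 14 | 233 | 249 |

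The 2018 window is 365 of 607 days, or 60% of the longer one.

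**Intervention rules at the edges.**
- A first visit on 1 January 2018 at weeks 7 to 4 means a pregnancy begun between 13 November and 4 December 2017. Both pregnancy-start rules exclude it, taking January 2018 as the start.
- A first visit on 28 February 2019 means a pregnancy begun between 10 and 31 January 2019. Pregnancies begun in February 2019 meet the 14-month rule but miss the visit window.
- A pregnancy begun on 31 December 2018 has its first visit between 28 January and 18 February 2019. The visit rule and the 12-month rule therefore nearly agree at the end.

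**First possible intervention birth.**
- First visit on 1 January 2018 at week 7: 33 weeks later, 20 August 2018.
- First visit on 1 January 2018 at week 4: 36 weeks later, 10 September 2018.
- Pregnancy start on 1 January 2018: 40 weeks later, 8 October 2018.

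**Share of each control window after that date.**

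| First birth | 20-month window | 2018 window |
|---|---|---|
| 20 Aug 2018 | 315/607 = 52% | 134/365 = 37% |
| 10 Sep 2018 | 294/607 = 48% | 113/365 = 31% |
| 8 Oct 2018 | 266/607 = 44% | 85/365 = 23% |

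**Ages at the overlap.** Every control child was born by 30 June 2017, before January 2018. The youngest would be about 14–15 months old at the first intervention births. The oldest intervention child would be about 10 months old at the end of June 2019.

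**Controls seen from November 2017 to August 2018.** 2 × 50 × 10/12 = 83.

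**The case against.** Much of the other side's case stands.

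- **The maternal half of the assurance is correct.** All index control pregnancies ended before the intervention began, under either window.
- **Exposure is not shown.** A reader might infer that late controls are partly treated and that the comparison is biased towards no effect by a calculable amount. Nothing in the document says that control children receive the intervention. They were past the first year when intervention births began, so the first-year feeding and vitamin D advice came too late for them. No intervention child would have reached the second-year advice by June 2019. Any percentage of dilution would need an exposure share that the document does not give.
- **The 2018 window is not infeasible.** A reader might infer that it cannot supply the controls. It yields the planned 100 before a loss that is already allowed for, or 107 at 320/6 births per quota. What it lacks is margin for refusals.
- **The intervention conflict is modest.** January 2018 to February 2019 is exactly 14 months, so 2.4 and 2.7 may describe one rule through two different events. The mismatch is a few weeks at the edges. Enrolment at the first paediatric visit, long before the outcome, also limits any choice made after results are seen.

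The objection does not remove the 8-month difference between the control windows, or the 12 against 14 months for pregnancy start. Nor does it make control measurement coincide with the start of the intervention. Routes for spill-over also exist in the text: unmasked paediatricians of the same unit collect control data, and the first workshop covers diet for the whole family, so a control child whose mother conceives again could be reached at home.

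**Conclusion.** The concern holds in a limited form. Group membership is not fixed by the document: the control pool is about 100 or about 167, the intervention pool about 200 or about 233, and the visit-based rule moves the edges by some weeks. This is a contradiction in stated text, not detail that an article leaves to a fuller document.

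The assurance in 2.4 is sound for the index pregnancies and unsupported, rather than shown to be false, for late-control infants. Between 44% and 52% of the 20-month window follows the first possible intervention birth. The shorter window does not escape, at 23–37%. These shares rest on 40-week pregnancies and on even accrual over the calendar. Whether spill-over occurs, and how large it would be, cannot be derived from the document.

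**What to change.** State one window per group, each tied to one event: the date of the 2-year visit for controls, and either the date of the first pregnancy visit or the date of pregnancy start for the intervention group. Use the same wording in the abstract, the specific objectives, 2.1, 2.4 and 2.7.

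If the 20-month control window is kept:
- flag control children whose mother entered the intervention programme before their 2-year visit;
- pre-specify a sensitivity analysis limited to controls measured before September 2018, about 83 available before refusals.

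Limit the statement that controls were not influenced to the index pregnancies and to that early subset.

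The cost is protocol wording, one flag from existing records, and one extra analysis with wider intervals.

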### 2.2. Study Population

The target population is two-year-old infants. The BHZ of Puerto Real (Cádiz) is constituted by two CMUs: Puerto Real, with four pediatric quotas and Casines, with two. The project will be developed in the CMU Puerto Real. There are no significant sociocultural differences between the different quotas. Since the number of births in the BHZ during the previous year was 320, it is expected that, on average, 50 newborns will be added annually to each quota. 

### 2.3. Masking 

Due to the characteristics of the study, it is not possible to blind it to the participants or to the researchers who will carry out the intervention. However, it will be masked for researchers, who will perform the evaluation of the effectiveness and analysis of the data. To do this, they will not know the coding of the randomization variable, which will be guarded. This way, it will not be possible for them to know which of the groups received the intervention until the analysis is completed.

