### 2.9. Data Collection 

The data for the control group will be collected through a data collection sheet, specifically designed for the study, from three sources: (1)Direct questions to the parents at the one-year and two-year visits, performed by paediatricians.(2)The weight, height and BMI records of the Diraya program, both for pregnant women and children.(3)Mothers and children’s medical records from the Diraya program. The form will be subsequently computerized.

The data for the intervention group will be collected in the same way, but also at the newborn and six-month visits, developed by paediatricians.

The midwives in the usual CPPCP controls will collect the gestational and delivery variables. Nurses and paediatricians in the usual controls of the A-CAHP will collect the somatometric variables of newborns up to 2 years.

After childbirth, during the puerperal visit, the midwife will register the birth data in the Diraya program as a hospital visit. If the mother does not attend the puerperal visit, it will be the paediatricians at the newborn visit who will collect the data from birth.

The weight and height of pregnant women will be measured with an ADE (GmbH & Co, Hamburg, Germany) scale, model M304641-01, with a reading range from 2 to 250 kg and a precision of 100 g, with an ADE stadiometer coupled to the scale, model MZ10023-1, with a reading range of 60–210 cm and a precision of 0.1 cm.

Weights will be measured in the first and second year of age with the child naked on a Soehnle baby scale, reading in a range of 0–20 kg with a 10 g precision. The length will be measured with the infant in supine position with a rigid Añó-Sayol stadiometer, with a reading range of 25 to 90 cm and an accuracy of 0.5 cm. The tables of weight, length and BMI values of the WHO will be used.

The skin folds will be measured with a Holtain Skinfold Caliper plicometer with an amplitude of 0–46 mm, 0.2 mm graduation and a constant pressure of 10 g/mm^2^. They will be measured in the left side of the body, in triplicate and by a single observer for each pediatric quote, according to universally recommended techniques [62,63].

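### The masking section rests on a randomization variable that a non-randomised trial does not have, and its absolute claim of masking is not supported

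*Protocol article*

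**What the plan says.** Section 2.3 first concedes that "it is not possible to blind it to the participants or to the researchers who will carry out the intervention". It then claims protection for a second set of people: "it will be masked for researchers, who will perform the evaluation of the effectiveness and analysis of the data". The stated means is that "they will not know the coding of the randomization variable, which will be guarded", and the stated result is absolute: "it will not be possible for them to know which of the groups received the intervention until the analysis is completed".

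Section 2.1 says "Randomization could not be carried out for ethical reasons" and that "a historical control group of the same population consisting of children who turn 2 years old during 2018 will be used". The Abstract calls the trial non-randomised, and section 2.11 names non-randomness as the main limitation.

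On who collects the data, the Abstract says "Data will be collected through a data collection sheet by the paediatricians". Section 2.9 has nurses and paediatricians take the children's body measurements up to age 2 at the usual health checks, with a single skinfold observer per paediatric quota. Section 2.4 adds that two paediatricians of the same unit collect the control data. The Introduction says that the usual primary care team delivers the intervention. No independent or masked assessor is described.

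**The concern.** Two things are wrong with the paragraph as written. The masking device it names cannot exist in this design. The guarantee built on that device also reaches further than a hidden group code could, because the control group is historical and calendar time separates the two groups completely.

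At stake is what the trial may claim. Percentage of fat mass at 2 years is the outcome named in the project's hypothesis, and the protocol collects skinfolds with a hand-held caliper, so observer expectation is a plausible route to bias. A reader who takes section 2.3 at face value could credit the result with blinded outcome assessment. Section 2.11 does not correct that impression, since it says nothing about open measurement.

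**Working it through.** The masking section gives no figure of its own to reproduce. The check is calendar arithmetic on the stated windows, followed by a reading of the two possible meanings of the claim.

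**Inputs**

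- Controls reach age 2 between November 2017 and June 2019 (Introduction, specific objectives). Section 2.1 gives calendar year 2018, which lies inside that window.
- Intervention pregnancies begin between January and December 2018 (Introduction). First pregnancy visits run from January 2018 to February 2019 (section 2.7) and take place in weeks 4 to 7.
- Planned sizes are 100 controls and 150 intervention children, with 15% loss (section 2.5).
- Assumptions: term birth = pregnancy start + 280 days. The extreme early case is a first visit on 1 January 2018 at week 7, with birth at 32 weeks.

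**Step 1: dates**

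| Group | Births | Age 2 |
|---|---|---|
| Control | Nov 2015 to Jun 2017 | Nov 2017 to Jun 2019 |
| Intervention, pregnancy start Jan to Dec 2018 | 8 Oct 2018 to 7 Oct 2019 | Oct 2020 to Oct 2021 |
| Intervention, pregnancy start to end Feb 2019 | 8 Oct 2018 to 5 Dec 2019 | Oct 2020 to Dec 2021 |
| Intervention, extreme early case | 25 Jun 2018 (1 Jan 2018 − 49 days + 224 days) | 25 Jun 2020 |

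From the last control birth (30 June 2017) to the first intervention birth is 15.3 months at term and 11.8 months in the extreme case. The windows do not overlap for births or for two-year measurements, so one date identifies the group.

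**Step 2: the measurers.** They work at routine visits within the quotas, during a period when every child reaching age 2 belongs to one group. They can know the group whether or not a code is guarded. Section 2.3 also concedes that those who carry out the intervention cannot be blinded, and the usual care team is among them.

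**Step 3: the analysts.** A group code hides the label. It does not hide the group if the file also holds birth dates or visit dates. A quota identifier tells part of the story too: controls come from two quotas and the intervention group from four, so if the two are among the four, the other two quotas hold intervention children only. After 15% loss the planned sizes are 100 × 0.85 = 85 and 150 × 0.85 = 127.5, so arbitrary labels can still be guessed from the counts.

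**Step 4: illustration only.** Suppose that open measurement shifts readings by 0.1 to 0.2 SD. This is an assumption; the document gives no such figure. With 85 and 127 children, the standard error in SD units is √(1/85 + 1/127) = 0.140. With no true effect, a two-sided 5% test rejects with probability Φ(−1.96 + d/0.140) + Φ(−1.96 − d/0.140):

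- d = 0.1: 0.11
- d = 0.2: 0.30

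**The case against.** The strongest defence is that section 2.3 never says the measurers are masked. It admits that those who carry out the intervention cannot be, and its phrase about evaluating effectiveness may mean the analysts alone. The non-randomised design is stated plainly elsewhere, so few readers would be misled about allocation, and the phrase randomization variable may be a slip for group code. This ambiguity stands. It does not rescue the paragraph, because the claim is false on one reading and too absolute on the other.

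Four stronger inferences are tempting, and the document does not support them.

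- *Newborn and six-month fields exist only for intervention children.* Section 2.9 says "The data for the intervention group will be collected in the same way, but also at the newborn and six-month visits". That describes extra collection occasions. Control data also come from medical and growth records, and section 2.8.1 lists newborn weight and early weight gain without limiting them to one group.
- *The analyst always knows the group, so the code conceals nothing.* That depends on what the analysis file contains, which the article does not say. Dates and quota are not among the variables listed in section 2.8.
- *The skinfold observer is the treating paediatrician.* Section 2.9 specifies one observer per quota without saying who it is. The calendar argument does not need this.
- *The false-positive rate is 11% to 30%.* Those figures follow from an assumed shift and make no allowance for the triplicate readings and standard technique in section 2.9. They illustrate open measurement in general and do not measure the fault in the text.

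**Conclusion.** The masking paragraph is wrong as written. It names a device that the design does not have, and it gives an unconditional assurance that the design cannot deliver. Outcome measurement is open in the sense that matters: the two-year windows are about 15 months apart at term and still about 12 months apart in the extreme early case, so the measurer can always know the group. That conclusion rests on the stated windows and on the birth-timing assumptions above. Analyst masking is possible in part, but only under file-handling conditions that the article does not state, and never to the point where knowing the group is impossible.

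The effect on the trial's estimate cannot be sized from the document. What changes is the claim that the trial may make about protection from detection and analysis bias.

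**What to change.** Rewrite section 2.3 and add a sentence to section 2.11:

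1. Delete the reference to a randomization variable.
2. State that delivery of the intervention and measurement of the two-year outcomes are both unmasked, and list this as a limitation beside non-randomness.
3. Claim at most partial masking of the analysts. Base it on an arbitrary group code in a file without birth dates, visit dates or quota identifiers, and acknowledge that the unequal sizes allow a guess. Derive any date-based variables before the dates are removed. Keep newborn weight and the weight-gain variables, which section 2.8.1 plans to use.
4. Freeze the analysis code before the intervention two-year data are merged. This protects the analysis even if the analyst guesses the group.

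No new rule making a fat-mass result depend on a BMI result is needed. BMI at 2 years is already a dependent variable, and such a rule would change how the hypothesis is judged, at a cost in power that has not been worked out.

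The cost is wording, one data-preparation step and a dated copy of the code. Data collection does not change. The trial gives up a blinding claim that it could not have sustained.
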